## Abstract

**Background:**

Physicians’ guideline use rates for diagnosis, treatment and monitoring of diabetes mellitus (DM) is very low. Time constraints, patient overpopulation, and complex guidelines require alternative solutions for real time patient monitoring. Rapidly evolving e-health technology combined with clinical decision support and monitoring systems (CDSMS) provides an effective solution to these problems. The purpose of the study is to develop a user-friendly, comprehensive, fully integrated web and mobile-based Clinical Decision Support and Monitoring System (CDSMS) for the screening, diagnosis, treatment, and monitoring of DM diseases which is used by physicians and patients in primary care and to determine the effectiveness of the system.

**Methods:**

The CDSMS will be based on evidence-based guidelines for DM disease. A web and mobile-based application will be developed in which the physician will remotely monitor patient data through mobile applications in real time.

The developed CDSMS will be tested in two stages. In the first stage, the usability, understandability, and adequacy of the application will be determined. Five primary care physicians will use the developed application for at least 16 DM patients. Necessary improvements will be made according to physician feedback. In the second phase, a parallel, single-blind, randomized controlled trial will be implemented. DM diagnosed patients will be recruited for the CDSMS trial by their primary care physicians. Ten physicians and their 439 patients will be involved in the study. Eligible participants will be assigned to intervention and control groups with simple randomization. The significance level will be accepted as *p* < 0.05. In the intervention group, the system will make recommendations on patient monitoring, diagnosis, and treatment. These recommendations will be implemented at the physician’s discretion. Patients in the control group will be treated by physicians according to current DM treatment standards. Patients in both groups will be monitored for 6 months. Patient data will be compared between 0th and 6th month of the study. . Clinical and laboratory outcomes will be assessed in person while others will be self-assessed online.

**Discussion:**

The developed system will be the first of its kind to utilize evidence based guidelines to provide health services to DM patients.

**Trial registration:**

ClinicalTrials.gov NCT02917226. 28 September 2016.

## Background

Diabetes mellitus (DM) is among the leading causes of morbidity and mortality worldwide. A study from the National Burden of Disease reports that cardiovascular diseases and diabetes rank first and ninth among causes of death, with mortality rates of 47.7% and 2.2%, respectively [1]. In 2009, The World Health Organization reported that the top three risk factors for mortality are, in order, high blood pressure, smoking, and high blood glucose [2]. Diabetes has a high prevalence and continues to increase worldwide over time.

According to a study by TURDEP II, 13.7% of the Turkish population has diabetes [3]. HbA1c is accepted as a marker for glycemic control criterion. Ratio of diabetic patients whose blood glucose is regulated is very low [3]. According to a study, the rate of diabetic patients whose HbA1c value is <7% were found only 30.1% [4].

Diabetes is one of the highest cardiovascular disease risk factors. If the disease is taken under control, morbidity and mortality rates of society reduce. Despite the high rate of DM prevalence, diagnosis of the disease is still around 13.7%. The diagnosis rate should be increased first to reduce morbidity and mortality caused by the DM disease. DM prevalence studies in Turkey have shown that halves rule is valid for the awareness, treatment and control rates of the disease [3].

Today, the purpose of treatment of chronic illness is not to heal the patient, but to enhance the adherence of the individual to the treatment program and to promote the life quality by cooperation. For this reason, the importance of protecting, maintaining and developing health has been emphasized over the treatment of disease, thus nurturing the concept of “self-care” [5].

Diabetes is a chronic health problem. Diabetes patients often face challenges throughout treatment, including emotional instability and difficulty adapting to lifestyle changes. Except for the natural distress caused by symptoms, complications and treatments, the patient’s future worries affect his cognitive and emotional functions and social life [6]. Self-efficacy beliefs play an important role in individuals with health problems like diabetes that require complex treatment and care, taking steps to make lifestyle changes and learning new skills to cope with the disease process. It is expected that diabetics should have sufficient self-efficacy to cope effectively with complex diabetes care and treatment. Diabetics‘self-care behaviors can be improved by increasing their self-efficacy levels [7, 8].

Guidelines used for DM management are prepared on the basis of evidence based studies conducted by experts both at the national and international level.

In DM management guidelines, the standards for diagnosing are specified and the requirements for differential diagnosis are systematized. [9]. Then the disease is classified according to the patient’s history, physical examination and laboratory data.

The guidelines suggest which patient risk factors should be evaluated and which tests should be completed. After diagnosis and differential diagnosis, treatment alternatives are suggested to the physician based on the guidelines set forth by the evidence-based studies. These guidelines include systematical treatment and follow-up process according to the diagnosis and prognosis. [9, 10].

Physicians’ guideline use rate in Turkey, as well as internationally, is very low. A study conducted in Turkey showed that diabetic patients are not treated according to current guidelines [11].

Periodic health care is a monitoring program formatted by risk factors, through screening, examination and testing of healthy people, counseling and health education. The program is evidence based, effective, feasible and acceptable. In this evidence based program, screening, case detection, immunization, chemoprophylaxis and counseling are defined clearly according to people’s age, sex and risk factors. Institutions that provide primary care carry out periodic health care services. Established guidelines require healthy adults to be periodically screened for health risk assessments. For example, the HbA1C test must be applied once every three to five years to patients with a high risk score, and once a year to those with a very high score [12].

Primary care providers play a vital role in the diagnosis, treatment and control of DM disease. The World Health Organization states that primary health care has a key role in reducing the morbidity and mortality of chronic diseases. Strengthening primary care is on the agenda of all countries for ensuring the control of chronic diseases. Therefore, adapting the physician’s approach to current DM management guidelines and developing a standard approach will provide significant gains in diabetes control. Control of diabetes will increase the length and quality of patient life. This will allow patients to apply less to primary health care providers. Thus, the time that physicians will allocate per patient will increase.

There are several computerized clinical decision support systems (CDSS) developed for management of chronical diseases [13]. There are a variety of uses of CDSS in primary care such as depression, hypertension and medication reviews [14–16]. In addition, various rule based and artificial intelligence based decision support systems have been developed for diabetes diagnosis [17, 18].

Mobile technologies are becoming important for providing individual-level support to health care users and promising platform for health interventions. In recent years, researchers have been using mobile phones as tools for encouraging physical activity and healthy diets [19], for symptom monitoring in asthma [20] and heart disease [21], reminding patients about upcoming appointments, supporting smoking cessation [22], and for a range of other health problems [23]. In addition, various kinds of m-health applications were developed for other purposes such as enabling users to log and chart data about their diet [24, 25], exercise [26, 27], blood glucose levels [28], and other health-related behaviors and measures [29–32]. Examples included patient terminals for tele-monitoring of conditions such as hypertension [33] and chronic heart failure [34] and applications that receive data from pedometers, blood pressure monitors and other devices [35]. On the other hand, some researchers [36] developed a diabetes support system using mobile phones, in which the user inputs information regarding his/her daily measures rather than using sensors.

### Study aim

The purpose of the study is to develop a user-friendly, comprehensive, fully integrated web and mobile-based Clinical Decision Support and Monitoring System (CDSMS) for the screening, diagnosis, treatment, and monitoring of DM diseases which is used by physicians and patients in primary care and to determine the effectiveness of the system.

The clinical decision support system is developed based on the rules obtained from evidence-based guidelines [10]. The web based system provides screening, diagnosis, and treatment suggestions to primary care physicians. For (tele) monitoring system, a mobile health application will be developed to collect patients’ measures both manually and via sensors.

## Methods

### Cdsms

The clinical decision support rule sets are built by three family medicine research academicians and a consultant cardiologist using evidence-based guidelines. Then, three computer engineering researchers develop a web and mobile based software using these protocols. This software will be used by physicians and patients. The software has been developed and it is currently in the testing process.

### Design and settings

The study design is a parallel single blind randomized controlled trial**.** The research will be conducted in Dokuz Eylül University (DEU) Family Medicine Outpatient Clinic and selected family medicine units in İzmir. DEU Hospital is a university hospital in Izmir, the third largest city in Turkey. The family medicine outpatient clinic provides primary healthcare services to outpatients in the DEU department of family medicine.

The family medicine units which provide primary health care are located widely in Izmir. There are 972 family medicine units in Izmir metropolis. They serve under Turkish Ministry of Health. In Turkey, electronic health record systems are used for the health care services of the family medicine units. These systems mainly records preventive health care services, disease diagnoses and drug related data. Because there is not a governmental obligation, these systems have not any evidence-based sets.

In this study, validation of the developed CDSMS will be done in two stages. In first stage, the understandability and usability and adequacy of the system will be tested. Necessary adjustments will be made in the program in accordance with feedbacks taken from physicians and patients who use the application.

In the second stage, effectiveness of CDSMS will be evaluated by conducting a parallel single blind randomized controlled trial. Consort schema [37] of the RCT is in Fig. 1.

**Fig. 1 Fig1:**
[figure not shown]
CONSORT Randomization Schema [37]

### Participants and sample size

The study population consists of patients applied to Dokuz Eylül University Family Medicine Clinics and family medicine units in İzmir. The CDSMS which is developed in this study will be validated in two stages. Different sample numbers and sampling methods will be used in each stage.

### Stage 1

In the first stage, understandability, usability and adequacy of CDSMS software will be tested. In this stage, two researchers from Department of Family Medicine and three physicians from other family medicine units will test CDSMS on at least 16 diabetes patients. Inclusion and exclusion criteria for stage 1 are listed below in Table 1. The CDSMS software test will be done on diabetes patients who apply for consultation. The physicians will perform patient interviews using the CDSMS. They will fill in feedback forms about program functionality and improvements needed. A Web Site Usability Test [38] and feedback form will be used to measure understandability, usability, and adequacy of CDSMS through user perception. The scale has 25 items. The answers to scale items are gathered with Likert type quintile rating scale. ISO/IEC 9126–1 (2001) defines usability as the capacity of the software product to be included/understood, learned, used and attractive to the user, when it is used under specified conditions. It characterizes the four attributes of usability as understandability, learnability, operability, and attractiveness of the software product. Understandability assesses whether new users can understand whether the software is suitable and how it can be used for particular tasks. Learnability assesses how long it takes users to learn to use particular functions, and the effectiveness of help systems and documentation. Operability assesses whether users can operate and control the software. Attractiveness metrics assess the appearance of the software, and will be influenced by factors such as screen design and color [39]. The feedback form will consist of open-ended questions and will be used to get feedback and suggestions from the users.

**Table 1 Tab1:** Inclusion and exclusion criteria

Inclusion Criteria	Exclusion Criteria
• Over age 40 • Volunteer • Computer and Internet literacy • DM diagnosed or having at least one of diagnostic criteria. These criteria; • HbA1c ≥ 6.5 • FPG ≥ 126 mg / dl • 2-h postprandial glucose ≥200 mg / dl • Any time postprandial glucose ≥200 mg / dl • Diabetes symptoms	• Having communication problems • Type 1 diabetes • MODY type DM • Psychotic disorders • Dementia

### Stage 2

In the second stage, the health data of 3000 participants will be evaluated to determine the effectiveness of CDSMS in screening. Participants who use medicine for DM treatment will be excluded from data analysis when measuring the effectiveness of the system in screening.

Patients who applied to primary health care services for any reason and screened within the scope of periodic health care for diabetes, having at least one measurement of FPG (Fasting Plasma Glucose), HbA1C or PPG (Postprandial Plasma Glucose) in last six months will be participants of stage 2. Participants determined in second phase will be evaluated in terms of inclusion and exclusion criteria. Eligible and volunteer participants will take part in the trial. Inclusion and exclusion criteria for randomized controlled trial are listed below in Table 1.

Patients who were diagnosed with DM among 3000 participants (new diagnosis, former diagnosis, medicine users, non-medicine users) will form the population of the randomized controlled trial. The sample size evaluated by significance level *p* = 0.05, 80% power, 25% prevalence (controlled diabetes) and odds ratio 2 will be included to experimental study. Because in RCT studies lost to follow up is approximately 15.0%, this amount is taken into account for determining the sample size. The sample contains 439 patients with 110 interventions and 329 control groups. The ratio of intervention to non-intervention (controls) is 1:3. About 3000 people over age 40 apply to the 10 primary health care units (In the city of Izmir in Turkey) in a month. For reaching expected number of samples, at least %14 of patients are thought to be eligible for inclusion criteria. (assuming DM prevalence approximately 14%).

Diabetes symptoms aforementioned in Table 1 are classical symptoms of polyuria, polydipsia, polyphagia or loss of appetite, weakness, fatigue, dry mouth, nocturia. Less common symptoms are blurred vision, unexplained weight loss, persistent infections, recurrent yeast infections and itching [10].

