### Procedure

#### Stage 1

In the first stage, understandability, usability and adequacy of CDSMS software will be tested. 5 physicians will test CDSMS on at least 16 diabetes patients. The system will be revised according to the comments received on the Web Site Usability Test [38] and feedback form.

#### Stage 2

At this stage, a randomized controlled trial will be performed. Firstly, the physicians who manage the treatment of the patients will register online through the web based portal for free. The researchers will train these physicians about the use of portal.

Patients who are referred to select family medicine centers for any reason will receive diabetes screening using CDSMS. The patients who were previously diagnosed as diabetics will be recruited for trial by the physicians. The recruited patients will register to the CDSMS via mobile phone or web page with the accounts provided by their physicians, free of charge.

The proposed clinical decision support system is a recommended tool for primary care physicians to make clinical decisions on screening, diagnosis, treatment and monitoring of DM patients. Physicians input the data of patients having FPG, HbA1c or PPG test results in last six months. CDSS will make a statement on diagnosis of patient and/or stage. The system will also suggest a treatment plan for the patient. The physician will evaluate the system’s recommendations and decide on a treatment for the patient and input his/her treatment decision. CDSS will suggest a monitoring plan to the physician. The physician will evaluate the proposals and input the monitoring plan that he/she has decided for the patient into the system. The follow-up visits will happen with the physician. There are two options for carrying out the monitoring process:

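### The Stage 2 population rules contradict each other: read literally, Table 1 admits a person to the RCT on symptoms alone, other text requires a diabetes diagnosis, and the screening analysis keeps known unmedicated diabetics

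*Protocol article*

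**What the plan says.** All statements are in the protocol article.

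**RCT entry**
- Participants and sample size, Stage 2, makes Table 1 the governing list: "Inclusion and exclusion criteria for randomized controlled trial are listed below in Table 1".
- Table 1 admits a person who is "DM diagnosed or having at least one of diagnostic criteria". The list of criteria ends with "Any time postprandial glucose ≥200 mg / dl • Diabetes symptoms". Symptoms form their own item, with no laboratory value attached.
- The Stage 2 text defines these symptoms broadly: "Diabetes symptoms aforementioned in Table 1 are classical symptoms of polyuria, polydipsia, polyphagia or loss of appetite, weakness, fatigue, dry mouth, nocturia".
- Stage 2 participants need a recent fasting, postprandial or HbA1c measurement, but no threshold is set for it.
- Under Allocation, nurses check eligibility and allocate from the lists.

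**Competing statements on the RCT population**
- The Stage 2 text gives the population as "Patients who were diagnosed with DM among 3000 participants (new diagnosis, former diagnosis, medicine users, non-medicine users").
- Procedure, Stage 2, says: "The patients who were previously diagnosed as diabetics will be recruited for trial by the physicians".
- The Methods part of the Abstract also speaks of recruiting patients with diagnosed diabetes.

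**Screening analysis**
- The only stated exclusion is: "Participants who use medicine for DM treatment will be excluded from data analysis when measuring the effectiveness of the system in screening".

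**The concern.** Table 1, the Stage 2 text and the Procedure section describe three different populations: anyone with a diagnosis or one listed criterion; anyone diagnosed, newly or earlier; and only those diagnosed earlier. The nurses at allocation need a single rule, and Table 1 is the one labelled as eligibility criteria.

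If Table 1 is applied as written, some randomised people may not have diabetes. They would count as controlled in either arm and have little room for HbA1c or glucose to fall, so they would shrink the contrast between the arms. The planning figures make no allowance for them.

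The screening analysis raises a different problem. Screening is meant to find unrecognised disease. The Stage 2 text itself recognises former diagnoses and non-users of medicine among the 3000, yet a known case not on medicine stays in the analysis.

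**Working it through.** **1. The population that the planning figures assume.** Two inputs presuppose that everyone randomised has diabetes: the 25% rate of controlled diabetes, and the estimate that about 14% of attenders are eligible, which the article takes from diabetes prevalence.

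**2. Reproducing the stated sample size.** Inputs from Stage 2: control rate p0 = 0.25, odds ratio 2, significance level 0.05 (two-sided assumed, as sidedness is not stated), power 80%, ratio 1:3, loss to follow-up 15%.
- Odds of control in the intervention arm = 2 × 0.25/0.75 = 0.667, so p1 = 0.667/1.667 = 0.40.
- Pooled rate = (0.40 + 3 × 0.25)/4 = 0.2875.
- Kelsey formula for the intervention arm: (1.960 + 0.842)² × 0.2875 × 0.7125 × (4/3) / 0.15² = 95.3, rounded up to 96. The control arm is 3 × 95.3 = 285.8, rounded up to 286. The total is 382.
- Times 1.15: 110 + 329 = 439, an exact match.

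**3. Effect of entrants without diabetes.** Let f be the share of randomised patients without diabetes, all counted as controlled in both arms. The document gives no value for f, so the values below are assumptions. In each arm the rate becomes p(1 − f) + f. Power = Φ{(difference − 1.96 × pooled standard error) / unpooled standard error}. It is shown for 110 against 329, and for 85% evaluable (93.5 in the intervention arm and three times that in control).

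| f | Control | Intervention | Odds ratio | Power, all 439 | Power, 85% evaluable |
|---|---|---|---|---|---|
| 0 | 25.0% | 40.0% | 2.00 | 0.84 | 0.78 |
| 5% | 28.8% | 43.0% | 1.87 | 0.78 | 0.72 |
| 10% | 32.5% | 46.0% | 1.77 | 0.72 | 0.65 |
| 20% | 40.0% | 52.0% | 1.63 | 0.60 | 0.53 |

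The f = 10% row with all 439: rates 0.46 and 0.325, difference 0.135, pooled standard error 0.0528, unpooled 0.0541. Then (0.135 − 1.96 × 0.0528)/0.0541 = 0.58, which gives power 0.72.

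The 0.78 at f = 0 in the last column comes from the loss to follow-up, not from eligibility. Only the fall down each column belongs to this point.

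**4. Screening.** The article states no screening metric, no reference standard and no share of known unmedicated cases, so no bias can be calculated.

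**The case against.** **The diagnosis text may already restrict entry.** The Abstract, the Stage 2 text and the Procedure section all require a diagnosis, and the 14% eligibility estimate makes sense only if eligible means diabetic. A reader might infer that the plan has settled on admitting people without diabetes. The documents do not support that: Table 1 is one side of a contradiction. The objection does not remove the conflict, however. Table 1 calls symptoms a diagnostic criterion, so a new diagnosis could rest on them, and the Stage 2 and Procedure texts still disagree on whether new diagnoses enter.

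**Table 1 has lost its layout.** The nesting of its items is flattened in the text available. Symptoms may have been meant to accompany the any-time glucose item. The separate bullet and the at-least-one wording point the other way, but some doubt remains.

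**The share f is assumed, and the endpoint differs.** Both points stand. If the diagnosis text prevails in practice, f could be near zero. The listed primary outcomes are HbA1c and glucose levels, analysed by a mixed model. The power figures therefore apply to the controlled-diabetes proportion behind the sample size, not to those analyses.

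**The screening estimate need not be inflated.** A reader might infer that known cases overstate performance, and might size this from the halves rule in the Background: 14% of 3000 is 420 cases, 210 aware, 105 of them untreated, so 105 of the remaining 315, or 33%. That applies a general remark as exact fractions to a group selected for a recent glucose test, and it gives a share of known cases, not a bias. Known cases counted as detections would raise the apparent yield. A known diabetic with normal values could be missed and lower the apparent sensitivity. If the measure were agreement between the system and the physician, known cases could be legitimate test cases.

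**Conclusion.** The contradiction is firm. Table 1 read literally, the Stage 2 text and the Procedure section define three different RCT populations, and only the versions that require a diagnosis match the sample size. It is not established that people without diabetes will be randomised, or in what number. The power losses in the table are conditional on an assumed share of 5% to 20%, on those entrants counting as controlled in both arms, and on a two-sided 0.05 test.

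The screening exclusion is incomplete as written, because it leaves known unmedicated diabetics in an analysis of screening effectiveness. This contaminates the estimate, but neither its direction nor its size can be stated from the document. The point should be corrected because it decides who is randomised and who is analysed.

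**What to change.** - Reconcile Table 1 with the Abstract, the Stage 2 text and the Procedure section, so that RCT entry requires a diabetes diagnosis, either existing or confirmed by one of the laboratory criteria already in Table 1. State that symptoms alone are not sufficient.
- State once whether newly diagnosed patients enter, and use the same wording in the Stage 2 and Procedure texts.
- Exclude everyone with a previous diabetes diagnosis from the screening-effectiveness analysis, not only medicine users, or report them separately.

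The cost is a few sentences, a slightly smaller eligible pool than literal Table 1 would allow, and a slightly smaller screening set. The article's own eligibility estimate already counts only people with diabetes (0.14 × 3000 = 420). Since 420 is below 439, the decision on new diagnoses should be made with recruitment in view.
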